##### Additional interventions

Community involvement in monitoring health services is an essential component of the NRHM programme. Village health and sanitation committees (VHSCs or VHCs) are mandated to monitor local services as well as disseminate information about rights and entitlements to healthcare. We will undertake three main activities related to strengthening health services in *both *intervention and control areas. First, we will carry out at least one village health committee meeting about rights and entitlements in each village during the study period. Second, we will organise meetings with government officials and hospital management committees to inform the provision of appropriate care for mothers and newborns in facilities in the study districts. Finally, we will carry out at least one meeting with ASHAs using the appreciative inquiry method [29] to strengthen their job motivation and help them further enhance their work performance.

#### Impact evaluation

##### Sample size

A sample size calculation was carried out in June 2010 using 11 months of available data on birth outcomes from the study areas prior to the creation of clusters. Baseline mortality data collected from the study areas between 1^st ^February 2009 and 31^st ^December 2009 indicated an NMR of 66 per 1000. We estimated *k *(the between cluster correlation coefficient) at 0.1 on the basis of data from the Ekjut trial as well as baseline data from the JOHAR trial areas. On the basis of surveillance from existing clusters, for an average cluster population of 5000, we expect an estimated 100 livebirths per cluster per year. We aim to assess the impact of the intervention using a total of 2 years of birth outcomes. We used formulae from Hayes and Bennett to estimate the power of the study [30]. Assuming a more conservative baseline mortality rate estimate of 55 per 1000, with 100 livebirths per cluster per year in 30 clusters, the study will have between 76.6% and 79.6% power to detect a 30% reduction in the NMR (from 55 per 1000 to 38.5 per 1000) over 24 months.

##### Surveillance

A monitoring team independent from the intervention team was established to collect information on births and deaths to women of reproductive age and on events during the antenatal, delivery and postnatal periods through a surveillance system adapted from a previous study, covering a total population of around 158,053 [31] and described in Figure 3. One key informant (a community member) reports all births and deaths to women of reproductive age to an interviewer. The informant is visited on a monthly basis by an interviewer from the surveillance team. The interviewer checks the report, pays the informant an incentive of Rs30 for an identification and another Rs 50 for conducting an interview with the identified mother around six weeks after the delivery. The collected questionnaires are examined by District Monitoring Coordinators with guidance from District Managers. Completed questionnaires are then entered into a database designed in Microsoft Access. Baseline data on birth outcomes were collected for a full year from 1^st ^September 2009 to 31^st ^August 2010.

**Figure 3 F3:**
[figure not shown]
**Trial vital events surveillance system**.

##### Data monitoring, masking and analysis plan

Due to the nature of the intervention, the intervention team or participants cannot be blinded to the allocation however the analysts will be blinded to the allocation for the data safety and monitoring board and until the definitive analysis is performed. The intervention and monitoring team hold their meetings on separate days, and the content of the intervention is not discussed with monitoring team members. We shall analyse data for the primary and secondary endpoints for a data safety and monitoring board (DSMB) to be held in late 2011. The DSMB will be undertaken according to the principles stated in the DAMOCLES statement [32]. We will carry out intention-to-treat analyses using individual level data, adjusting for clustering using either logistic regression with random effects or generalised estimating equations [33]. In this data safety and monitoring board we will analyse data for the period from 1^st ^September 2010 till 31^st ^June 2011 (10 months of data). The DSMB will have three objectives:

(1) To report on the observed number of livebirths and neonatal mortality rate in the trial area in order to examine whether the original sample size calculation is robust; if the expected number of livebirths has not been reached the DSMB may recommend extending the trial;

(2) To assess the comparability of trial arms by examining data on the socio-economic characteristics of participants and clusters at baseline, including the coverage of home visits, in order to define any adjustments to be made in the final analysis;

(3) To examine available data for the primary and secondary endpoints in order to decide whether to continue or stop the trial

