**Methods/design:**

The study is a cluster-randomised controlled trial and will be implemented in five districts, three in Jharkhand and two in Orissa. The unit of randomisation is a rural cluster of approximately 5000 population. We identified villages within rural, tribal areas of five districts, approached them for participation in the study and enrolled them into 30 clusters, with approximately 10 ASHAs per cluster. Within each district, 6 clusters were randomly allocated to receive the community intervention or to the control group, resulting in 15 intervention and 15 control clusters. Randomisation was carried out in the presence of local stakeholders who selected the cluster numbers and allocated them to intervention or control using a pre-generated random number sequence. The intervention is a participatory learning and action cycle where ASHAs support community women's groups through a four-phase process in which they identify and prioritise local maternal and newborn health problems, implement strategies to address these and evaluate the result. The cycle is designed to fit with the ASHAs' mandate to mobilise communities for health and to complement their other tasks, including increasing institutional delivery rates and providing home visits to mothers and newborns. The trial's primary endpoint is neonatal mortality during 24 months of intervention. Additional endpoints include home care practices and health care-seeking in the antenatal, delivery and postnatal period. The impact of the intervention will be measured through a prospective surveillance system implemented by the project team, through which mothers will be interviewed around six weeks after delivery. Cost data and qualitative data are collected for cost-effectiveness and process evaluations.

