### Selection of clusters and unit of randomisation

The trial area covers a population of approximately 158,053 (based on 2001 Indian Census data) in three districts of Jharkhand (Ranchi, Khunti and Godda) and two districts of Orissa (Mayurbhanj and Rayagada). The location of study areas is shown in Figure 1 and district characteristics in Table 2. The unit of randomisation is a rural geographic cluster of approximately 5000 population. Within each district, the intervention team mapped villages and formed 6 clusters constituted of 5-8 villages and their neighbouring hamlets, with at least 10 active ASHAs per cluster. Within each district, 6 clusters were randomly allocated to receive the community intervention or to the control group, as described in Figure 2. Intervention and control clusters are separated either by natural boundaries (rivers or hills), or by 'buffer villages' not enrolled in the trial.

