##### Stopping rules

Because previous trials of women's groups in Nepal and eastern India have shown a strong effect of groups on neonatal mortality, we aim to stop the trial and introduce groups into the control area after the DSMB if we observe a reduction in the NMR of 40% or more after adjusting for differences observed at baseline, or if we observe a reduction inferior to 40% but with improvements in secondary indicators (home care or care seeking practices) consistent with a reduction, and satisfactory implementation quality indicators (70% or more of ASHAs have conducted all meetings at the time of the DSMB; % of women who gave birth in the study area who received information from a group member; % of women of reproductive age in group meetings).

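### Clusters were randomised within five districts, but the stated analysis has no district term, leaves the model open, and defers covariates to an interim review that also sees outcomes

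*Protocol article*

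**What the plan says.** Allocation was stratified. Under Selection of clusters and unit of randomisation: "Within each district, 6 clusters were randomly allocated to receive the community intervention or to the control group". The abstract gives the outcome: "resulting in 15 intervention and 15 control clusters". Randomisation and allocation describes a separate draw in each district from twenty numbered sequences. Twenty is the number of ways to choose 3 clusters from 6, which fits a 3:3 split in each district.

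The analysis is set out in Data monitoring, masking and analysis plan: individual-level data, intention to treat, "adjusting for clustering using either logistic regression with random effects or generalised estimating equations". No rule for choosing between the two models is given, and district does not appear.

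Adjustment for covariates is foreseen but not defined. The board's second objective is to judge the comparability of the arms by "examining data on the socio-economic characteristics of participants and clusters at baseline, including the coverage of home visits", and to do so "in order to define any adjustments to be made in the final analysis". Its third objective is to examine the primary and secondary endpoints and decide whether to continue. Stopping rules has the interim effect assessed "after adjusting for differences observed at baseline".

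Baseline mortality is available. Under Surveillance: "Baseline data on birth outcomes were collected for a full year from" September 2009 to August 2010. Baseline cluster mortality is not named as a covariate, and nothing excludes it.

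**The concern.** Stratifying by district removes district differences from the comparison of arms by design. If the model omits district, those differences stay in the between-cluster variance, so the standard error is larger than the design warrants. The intervals are then too wide, and power is lost in a trial planned at just under 80%. The article gives some reason to expect districts to differ. They lie in two states, the maternity incentive scheme has higher coverage in Orissa (Setting), and the number of ASHAs per district runs from 42 to 104 (Table 2).

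Two further points are left open. With 15 clusters per arm, the model and its standard-error method affect the test, so an unresolved choice allows more than one primary result. And the covariates are to be settled at a meeting that also has outcome data. The interim data run from September 2010 to June 2011, so January to June 2011, six of the 24 months in the primary analysis, will already have been examined.

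**Working it through.** **Inputs.** From Sample size: rates of 0.055 and 0.0385, k = 0.1, and "with 100 livebirths per cluster per year in 30 clusters", hence n = 200 per cluster over 24 months. Clusters per arm: c = 15. Two-sided alpha of 0.05 is assumed, as the article does not state it.

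**Stated power.** The Hayes and Bennett unmatched formula gives power = Φ(√[(c − 1)(p0 − p1)²/V] − 1.96), with V = p0(1 − p0)/n + p1(1 − p1)/n + k²(p0² + p1²).

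- V = 0.00025988 + 0.00018509 + 0.00004507 = 0.00049004
- (p0 − p1)² = 0.0165² = 0.00027225
- √(14 × 0.00027225/0.00049004) = 2.789, and Φ(2.789 − 1.960) = 79.6%

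This matches the upper stated figure. The lower figure, 76.6%, would need k of about 0.136 or fewer births; the article does not say which input was varied. Read as an intraclass correlation, 0.1 would give about 10% power, so k acts as a coefficient of variation (CV). The article does not say whether it is variation within districts or in total.

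**Type I error in closed form, equal clusters.** An uncorrected sandwich variance is too small by the factor (residual df)/30.

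- Treatment only: P(|t28| > 1.96 × √(28/30)) = P(|t28| > 1.894) = 6.9%
- Treatment plus four district terms: P(|t24| > 1.96 × √(24/30)) = P(|t24| > 1.753) = 9.2%

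**Simulation.** 40,000 runs per cell, five districts with 3 + 3 clusters of 200 births, control rate 55 per 1000, lognormal cluster effects, within-district CV 0.1. The between-district CV is an assumption. Power is for a rate ratio of 0.70. Ranges cover repeated runs.

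| District CV (assumed) | Size: uncorrected sandwich z, no district | Size: stratified cluster-level t, 24 df | Power: unstratified t, 28 df | Power: stratified t, 24 df |
|---|---|---|---|---|
| 0 | 6.7–6.9% | about 5% | about 80% | about 79% |
| 0.1 | 5.8–6.1% | about 5% | about 77% | about 79% |
| 0.2 | 3.7–3.8% | about 5% | about 71% | about 79% |
| 0.3 | 2.3–2.4% | about 5% | about 60% | about 78% |

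Adding district terms with an uncorrected sandwich gives 9.1–9.5% throughout, in line with the closed form.

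**If k = 0.1 is the total variation.** With the variance split equally within and between districts, unstratified power is 80.7% and stratified power 81.4%, a loss of 0.7 points. In the extreme case, with all the variation between districts, the figures are 81.0% and 82.8%.

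**Cost of stratifying when districts do not differ.** The noncentral t gives 79.6% on 28 df and 79.1% on 24 df, about half a point.

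**Baseline cluster mortality.** With about 100 births per cluster in the baseline year, its reliability at k = 0.1 is k²p²/[k²p² + p(1 − p)/100] = 0.00003025/(0.00003025 + 0.00051975) = 0.055. The precision to be gained from it is small.

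**The case against.** The strongest reply is that the article gives its method in one sentence. Stratum terms, named covariates and small-sample corrections are commonly left to a statistical analysis plan, which is not shown. That stands for the small-sample correction: its absence is not a fault in itself, and it matters here only because the remedy needs it. It stands less well for the model, where the text expressly offers two alternatives, and for the covariates, where the text fixes the timing of the decision.

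Four stronger readings are tempting and are not supported.

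- *The analysis adjusts for clustering only and ignores baseline.* The board's second objective and the stopping rule both foresee baseline adjustment. What can be criticised is that it is undefined and settled at the interim review. Leaving out baseline mortality would not invalidate the standard error.
- *The plan uses uncorrected GEE.* The article is silent on this.
- *The error bars must be wrong in one direction or the other.* For uncorrected GEE the two effects nearly cancel at a district CV of 0.1. For random-effects logistic regression with a Wald z-test and no district term, a simulation of 3,000 null runs per scenario gave 4.6–4.8% at a district CV of up to 0.1, which is essentially nominal.
- *Power is really 60–71%.* Those figures add an assumed district CV of 0.2–0.3 to k = 0.1, for a total CV of √(0.1² + 0.2²) = 0.22 to √(0.1² + 0.3²) = 0.32. That is two to three times the only variance figure in the article.

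The analysts are also blinded to allocation until the definitive analysis. This lowers the risk of a choice driven by results, but does not replace naming the model and covariates in advance. At k = 0.1 the two models' odds ratios differ by under 0.2% on the log scale, so the open choice matters for the standard error and test rather than for the estimand.

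**Conclusion.** The point holds in a limited form. Allocation was stratified by district; the stated analysis does not name district, does not choose its model, and leaves covariates to a meeting that also sees outcomes. The consequence depends on a district variance the article does not give. The loss of power is negligible to small if k = 0.1 is total variation, about 2 points at an added district CV of 0.1, about 8 at 0.2 and 18–19 at 0.3. In the other direction, an ordinary sandwich z-test would run at about 7% if districts do not differ. A stratified analysis with a small-sample method holds about 5% in every scenario tried. The results assume two-sided 5%, equal cluster sizes, a 3:3 split per district and lognormal cluster effects. The change is worth making because it costs almost nothing, not because the stated analysis has been shown to be invalid.

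**What to change.** Name one primary model, with district as a fixed effect and a stated small-sample method. One example is GEE with a bias-corrected sandwich (such as Kauermann–Carroll) and a t reference on about 24 df, fewer if cluster-level covariates are added. District terms should not be added with an uncorrected sandwich, which would give about 9% type I error. Make random-effects logistic regression the sensitivity analysis, or the reverse, but state which. List the adjustment covariates before any outcome data are reviewed, and limit the board's comparability review to description. Baseline cluster mortality may be included as a regression covariate, with little gain expected at k = 0.1; it should not be subtracted in full. If a separate analysis plan already settles these points, a cross-reference is enough. The cost is wording, since no new data are needed, and about half a point to one point of power if districts do not differ.

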##### Stopping rules

Because previous trials of women's groups in Nepal and eastern India have shown a strong effect of groups on neonatal mortality, we aim to stop the trial and introduce groups into the control area after the DSMB if we observe a reduction in the NMR of 40% or more after adjusting for differences observed at baseline, or if we observe a reduction inferior to 40% but with improvements in secondary indicators (home care or care seeking practices) consistent with a reduction, and satisfactory implementation quality indicators (70% or more of ASHAs have conducted all meetings at the time of the DSMB; % of women who gave birth in the study area who received information from a group member; % of women of reproductive age in group meetings).

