### Trial endpoints

The trial's primary endpoint is the neonatal mortality rate over 24 months. Because we expect a short lag period for this intervention to take effect as groups take some time to discuss the causes of maternal and newborn health problems before implementing strategies, we will include data for the last 24 months of the study (1^st ^January 2011 - 31^st ^December 2012) in the final analysis for the primary endpoint, thereby allowing for a four month lag-period. Additional endpoints for the trial include home care practices and health-care seeking behaviour for mothers and newborns and ASHAs' activities related to home visits. The trial endpoints are listed in Table 1.

**Table 1 T1:** Trial outcomes and indicators

Mortality	
Neonatal mortality rate	Number of Neonatal deaths per 1000 livebirths

Stillbirth rate	Number of Stillbirths per 1000 births

Early neonatal mortality rate	Number of early neonatal deaths (0-6 days) per 1000 livebirths

Late neonatal mortality rate	Number of late neonatal deaths (7-28 days) per 1000 livebirths

Maternal mortality ratio	Number of maternal deaths per 100 000 livebirths

Pregnancy-related mortality ratio	Number of pregnancy-related deaths per 100 000 livebirths

Perinatal mortality rate	Number of perinatal deaths per 1000 births

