##### Benefits to the control communities

Because the women's group intervention has demonstrated an impact on neonatal mortality in a similar setting, we have put in place stopping rules in order to introduce the intervention to control areas if positive results are observed at the first data safety and monitoring board. In addition, activities such as strengthening of Village Health Committees and Appreciative Inquiry workshops with ASHAs will be conducted in both intervention and control clusters.

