##### Sustainability and scalability

One key objective of the study is to identify mechanisms for scaling up the intervention. We will share implementation plans and findings with NRHM implementers in Jharkhand and Orissa. The intervention will be introduced immediately into the control areas if a positive impact is observed at the first Data Safety and Monitoring board. We shall invite a representative of the Indian Council of Medical Research to join the data safety monitoring group.

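### The second limb of the stopping rule sets no minimum mortality reduction and no statistical bound, so any observed fall in NMR below 40% meets its mortality condition

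*Protocol article*

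**What the plan says.** The Stopping rules section says that "we aim to stop the trial and introduce groups into the control area after the DSMB" under either of two limbs.

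- **Limb 1:** "if we observe a reduction in the NMR of 40% or more after adjusting for differences observed at baseline".
- **Limb 2:** "if we observe a reduction inferior to 40% but with improvements in secondary indicators (home care or care seeking practices) consistent with a reduction". This limb adds a third condition, that delivery of the intervention is judged satisfactory. One of its indicators has a threshold: at least 70% of ASHAs must have held every meeting due when the DSMB convenes. The other two (women who gave birth and received information from a group member; women of reproductive age in group meetings) have no cut-off.

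Neither limb carries a p-value, confidence limit or alpha boundary. Limb 2 does not say how many practices must improve, or by how much.

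The interim data run from 1 September 2010 to "June 2011 (10 months of data" (Data monitoring, masking and analysis plan). The primary analysis uses 1 January 2011 to 31 December 2012, "thereby allowing for a four month lag-period" (Trial endpoints).

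Two passages under Ethical issues describe the same intention more generally: "if positive results are observed at the first data safety and monitoring board" (Benefits to the control communities) and "The intervention will be introduced immediately into the control areas if a positive impact is observed at the first Data Safety and Monitoring board" (Sustainability and scalability).

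**The concern.** Read together, the two limbs cover every observed reduction above zero. Once the practice and implementation conditions are judged to be met, the 40% figure does no work, because a 1% reduction qualifies as well as a 39% one.

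Those other conditions cannot stand in for mortality evidence. The practices are reported by mothers about six weeks after delivery. Participants are not blinded, and several of the practices are topics of the group meetings (thermal care, hygiene, birth preparedness, care-seeking). They could improve, or be reported as improved, with no change in mortality. The implementation indicators measure delivery and reach of the groups.

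Meeting the rule takes the intervention into the control clusters, which ends the randomised comparison for the rest of the 24-month window. The protocol's justification for a randomised design is that this intervention has not been tested when delivered by community health workers. Stopping on an estimate compatible with no effect would leave that question open.

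**Working it through.** **Inputs.** From Sample size: control NMR 55 per 1000, reduced to 38.5 (30%); k = 0.1; 30 clusters, so c = 15 per arm; 100 livebirths per cluster per year. Alpha is not stated; two-sided 5% is assumed.

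**1. Reproduce the stated power.** The Hayes-Bennett unmatched formula for proportions gives z = √[c′(p0 − p1)² / V] − 1.96, where V = p0(1 − p0)/m + p1(1 − p1)/m + k²(p0² + p1²).

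- With m = 200 (24 months): V = 0.000260 + 0.000185 + 0.000045 = 0.000490, and (p0 − p1)² = 0.000272.
- c′ = c − 1 = 14: z = 2.789 − 1.960 = 0.829, power 79.6%.
- c′ = c − 2 = 13: z = 2.687 − 1.960 = 0.727, power 76.7%.

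The stated range is 76.6% to 79.6%, so the model matches the protocol's to within rounding.

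**2. Information at the interim.** 15 clusters × 100 × 10/12 = 1,250 livebirths per arm, or about 69 neonatal deaths per arm with no effect.

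**3. How often limb 2's mortality condition is met.** 200,000 trials were simulated per scenario, with gamma-distributed cluster rates (k = 0.1), binomial deaths and 83 livebirths per cluster.

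| True rate ratio | Observed reduction ≥ 40% (limb 1) | Observed reduction between 0 and 40% (limb 2 mortality condition) |
|---|---|---|
| 1.0 | about 0.2% | about 48% |
| 1.1 | about 0.02% | about 27% |

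With a control NMR of 66, the baseline figure in Sample size, the limb 2 column becomes about 49% and 25%. Using only the six interim months after the lag, at NMR 55, it becomes about 47% and 30%.

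**4. Precision of qualifying estimates.** Var(log RR) = (1 − p0)/(n p0) + (1 − p1)/(n p1) + 2k²/15, with n = 1,250, p0 = 0.055 and p1 = 0.055 × RR.

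- RR 0.90: 0.01375 + 0.01536 + 0.00133 = 0.03044, SE 0.174, 95% CI 0.64 to 1.27, p = 0.55.
- RR 0.80: 0.01375 + 0.01738 + 0.00133 = 0.03246, SE 0.180, 95% CI 0.56 to 1.14, p = 0.22.
- RR 0.69: SE 0.188, p = 0.048.

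The first two meet limb 2's mortality condition and are compatible with no effect. So does every other observed reduction short of about 31%.

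**5. Overlap with the lag.** September to December 2010 is four of the ten interim months. The primary analysis excludes those months because the groups need time to take effect.

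**6. What remains if controls are treated from the end of 2011.** January to December 2011 gives m = 100: V = 0.000520 + 0.000370 + 0.000045 = 0.000935. Power for a 30% reduction is 52.4% with c − 1 and 49.4% with c − 2.

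**The case against.** Several stronger readings are tempting, and the article does not support them.

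- **Improved practices alone would end the trial.** They would not. Limb 2 needs an observed reduction, improved practices and satisfactory implementation together.
- **A null intervention has a 48% chance of stopping the trial.** The 48% concerns one of three conditions. The probability of stopping cannot be computed, because the other conditions largely lack thresholds. For the same reason no chance figure should be attached to the practice indicators: the rule names no test for them and asks for improvements in the plural.
- **Any limb 2 stop would rest on no mortality evidence.** Observed reductions of about 31% to 39% fall under limb 2 and are nominally significant at 5%. The trial could stop on a null-compatible estimate; it need not.
- **The Ethical issues passages create a third, looser trigger.** The passage on benefits to control communities refers to the stopping rules already put in place, and the one on sustainability restates the same intention. They read as lay summaries, though their wording is looser than the rule.
- **Interim error is uncontrolled.** The article states no control. A DSMB charter or analysis plan may supply it.

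The rule is also phrased as an aim. The DSMB is to follow DAMOCLES principles, and the interim analysis adjusts for clustering, so some discretion remains. There is an ethical case for early roll-out, since earlier women's group trials showed strong effects.

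These points limit the claim but do not remove the fault. A rule is stated, and its second limb has no mortality threshold. Discretion is not a substitute for one, and the cluster-adjusted analysis is not tied to any decision boundary.

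**Conclusion.** Wrong as written. This is a badly fixed rule and not a detail left to another document. Any observed NMR reduction below 40% satisfies limb 2's mortality condition, which under no effect is close to a coin toss (about 48%) and under a true 10% increase in mortality still holds about 27% of the time. Whether the trial then stops depends on unblinded, interview-reported practices and on delivery indicators. Acting on it from the end of 2011 would cut power for the design effect from 76.6%–79.6% to about 49%–52%.

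Limb 1 is a lesser matter. Its chance of being met under no effect is about 0.2% on the ten interim months, although it too lacks a stated interval.

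The figures assume NMR 55 per 1000, k = 0.1, 100 livebirths per cluster-year, equal cluster sizes, two-sided 5%, and unadjusted rate ratios with no allowance for district stratification or baseline adjustment.

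**What to change.** Before the late-2011 DSMB meeting, amend the Stopping rules section:

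1. Remove the limb for reductions below 40% as a trigger, or make it conditional on the cluster-adjusted NMR estimate crossing a statistical boundary specified in advance and chosen with the DSMB.
2. Attach the cluster-adjusted estimate and its confidence interval to the 40% limb.
3. Give the practice and implementation indicators to the DSMB as supporting context only.
4. Have the two Ethical issues passages refer to this one rule.

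The choice of boundary is a real trade-off. A very strict one, such as two-sided p < 0.001, would need an observed reduction of about 50% at this sample size (RR 0.50 gives p = 0.0009). That is more than the 45% reported in the earlier Ekjut trial, so it would nearly rule out early stopping.

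The cost is a short protocol or charter amendment and a lower chance of early roll-out to the control clusters.
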